### **2.5.2 Handling of dropout cases**

After a subject drops out, the investigator should maintain contact with the subject, inquire about the reasons for dropout, record the last medication administration time, and make the dropouts complete as many assessment items as possible. Then the CRF should be completed. If someone withdraws due to allergic reactions, adverse events, or ineffective treatment, the investigator should provide appropriate treatment measures and some form of financial compensation to ensure the subject's rights.

All enrolled cases, regardless of dropout status, should have their data recorded and retained in the CRF. These records are essential for the Full Analysis Set (FAS) analysis. Dropout cases do not need to be supplemented separately.

## ***2.6 Termination criteria***

- 1) Discovery of severe safety issues during the trial.
- 2) The efficacy of the test drug is poor or even ineffective.
- 3) Identification of major errors in the study protocol or important deviations in its implementation, making it difficult to evaluate the drug's efficacy.
- 4) Request for trial termination by the sponsor due to financial reasons or management issues.

## **3. Study design**

This study is designed as a multicenter, randomized, double-blind, placebo-controlled trial.

### **3.1 Multicenter**

This study is simultaneously conducted at 3 centers: Xiyuan Hospital of China Academy of Chinese Medical Sciences; Guan'anmen Hospital of China Academy of Chinese Medical Sciences; Beijing Tongren Hospital Affiliated to Capital Medical University.

### **3.2 Randomization.**

Stratified and block randomization methods are employed. SAS statistical software is used to generate the 'Center Code Randomization Table' based on the number of cases from participating units and the randomization ratio. The selected block length, randomization seed parameters, and other confidential data were sealed in the blind envelope. Unrelated personnel encoded the drugs according to this randomization table. The intervention group and control group are allocated in a 1:1 ratio.

### **3.3 Control**

Placebo-controlled.

### **3.4 Sample size calculation**

The sample size is calculated based on the estimated post-treatment CT-FFR values. The PROMISE study revealed an average CT-FFR value of  $0.77 \pm 0.1$  for patients with ICL. A clinical study indicated that after traditional Chinese medicine intervention, patients with CAD had CT-FFR values of  $0.92 \pm 0.16$ . Therefore, it was assumed that the CT-FFR value in the control group is 0.77 and the value in the intervention group could be elevated to 0.92 after treatment, the standard deviation  $\sigma = 0.13$  for both two groups. Results from the NXT study indicated that for every 0.05 unit decrease in CT-FFR, there was an independent correlation with the increasing rate of composite cardiovascular events. Based on this, we have set the cut-off value  $\Delta=0.03$  in this superiority trial. The number of cases in the two groups is arranged in a ratio of 1:1, so  $c=1$ . Given a type I error rate of  $\alpha = 0.05$  (two-side test), a power of 95% (type II error rate of  $\beta = 0.05$ ), so  $u_\alpha=1.96$ ,  $u_\beta=1.64$ ,  $n_1=n_2\approx 55$ . Considering the maximum dropout rate of 10%, a total of 120 patients is needed. The calculation formula is as follows:

$$n_1 = \left(\frac{1+c}{c}\right) \left[\frac{(u_\alpha + u_\beta) \sigma}{\mu_T - \mu_C - \Delta}\right]^2 + \frac{1}{4} u_\alpha^2, \text{ and } n_2 = c n_1$$

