## **9. Statistical Analysis**

All statistical tests will be conducted as two-tailed tests, and a P-value  $\leq 0.05$  will be considered statistically significant for the tested differences.

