#### 9.2.2 Efficacy Analysis

- 1) Primary Efficacy Outcome: CT-FFR.
  - Description: CT-FFR values of the target vessels at baseline and 6 months after

treatment, as well as the difference from baseline to 6-month will be described. For multiple vessel lesions, the CT-FFR value of the most severely narrowed vessel will be selected.

- Intergroup Comparison: A linear mixed model will be used for comparison between groups. The dependent variable is the difference in CT-FFR from baseline to 6-month. Fixed effects include group and center, while random effects include subjects. Covariates include baseline values of CT-FFR, age, gender, BMI, systolic blood pressure, diastolic blood pressure, LDL-C, FBG, smoking status, alcohol consumption, family history of early-onset cardiovascular disease, presence of cerebrovascular disease, peripheral vascular disease, diabetes mellitus, hypertension, dyslipidemia, and concomitant use of PCSK-9 inhibitors.
  - Estimation: The least squares method will be used to estimate mean differences and 95% confidence intervals (CI).
- 2) Secondary Efficacy Outcomes
- a) Coronary imaging assessment indicators
- Description: %DS measurement will use the most narrowed location as the result; CACS and Gensini scores will use the total score as the result. Values of %DS, CACS, and Gensini scores at baseline and 6 months after treatment, as well as the difference from baseline to 6-month will be described.
  - Intergroup Comparison. A linear mixed model will be used, with the dependent variable being the difference from baseline to 6-month. Fixed effects include group and center, random effects include subjects, and covariates include baseline values.
  - Estimation: The least squares method will be used to estimate the mean difference and 95% CI.
- b) SAQ score
- Description: SAQ scores at baseline, 2, 4, and 6 months after treatment will be described, along with the differences from baseline to 2, 4, and 6 months.
  - Intergroup Comparisons: A mixed model for repeated measures will be used, with the dependent variable being the difference in SAQ scores at 2, 4, and 6 months relative to baseline, with the primary assessment time point at 6 months after treatment. Fixed effects include group and center, random effects include subjects. Covariates include baseline SAQ scores, visit times, the interactions between baseline and visit, and the interactions between treatment group and visit.

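### Section 3.4 sizes the trial for superiority by 0.03 CT-FFR, but no stated rule for the primary analysis uses that margin

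*Protocol*

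**What the plan says.** **Sizing (Protocol 3.4).** The calculation assumes that "the CT-FFR value in the control group is 0.77" and that "the value in the intervention group could be elevated to 0.92 after treatment", with "the standard deviation $\sigma = 0.13$ for both two groups". It then says "we have set the cut-off value $\Delta=0.03$ in this superiority trial", and supports the value by citing a study that linked decrements of 0.05 in CT-FFR to cardiovascular events. The printed formula divides by the expected difference minus Δ. Alpha is 0.05 two-sided and power is 95%. The stated result is about 55 per group, and 120 patients in total after allowing for 10% dropout.

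**Analysis (Protocol 9 and 9.2.2).** Section 9 says "All statistical tests will be conducted as two-tailed tests" and sets significance at P ≤ 0.05. For CT-FFR, section 9.2.2(1) says "A linear mixed model will be used for comparison between groups". It names the dependent variable (change from baseline to 6 months), the fixed and random effects and a long covariate list, and it asks for mean differences with 95% confidence intervals. It states no null value, and the margin of 0.03 does not reappear.

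**The concern.** A sample size formula with Δ subtracted in the denominator powers the hypothesis that the treatment difference exceeds Δ. A two-tailed P-value for a group effect in a linear mixed model tests a difference of zero unless a shifted null is specified. The sizing and the stated test therefore address different hypotheses.

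CT-FFR is the only primary efficacy outcome, so what the trial may conclude is at stake. A result can be significant under section 9 and still be compatible with benefits smaller than the cut-off in section 3.4. The protocol does not say how such a result should be described, so the choice could be made after the data are seen.

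**Working it through.** **Inputs, all from Protocol 3.4.** Means 0.77 and 0.92 (difference 0.15), Δ = 0.03, SD 0.13, 1:1 allocation, u = 1.96 and 1.64, total 120, dropout 10%.

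**1. The plan's own figure.** n = 2 × [(1.96 + 1.64) × 0.13 / (0.15 − 0.03)]² + 1.96²/4 = 2 × 3.9² + 0.96 = 31.4, so 32 per group. The stated 55 is not reproduced. An effective difference of 0.09 would give 2 × 5.2² + 0.96 = 55.04. This is a separate error. The steps below use only the planned total and the SD.

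**2. Standard error.** Evaluable patients per arm: 120 × 0.9 / 2 = 54. SE = 0.13 × √(2/54) = 0.0250.

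**3. Two thresholds for the observed difference.**
- Significant against zero: 1.96 × 0.0250 = 0.049.
- Lower 95% limit above 0.03: 0.03 + 0.049 = 0.079.

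Results between 0.049 and 0.079 meet the section 9 rule without showing superiority by the margin.

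**4. True difference exactly 0.03.**
- Test against zero, in favour of QXJYG: Φ(0.03/0.02502 − 1.96) = Φ(−0.761) = 22%.
- Test against the margin: 2.5% by construction.

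**5. Power of the margin test at the assumed 0.15.** Φ(0.12/0.02502 − 1.96) = Φ(2.84) = 99.8%. This exceeds the stated 95% because the planned number is well above the 32 per group that the formula gives.

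**6. Chance of landing between the thresholds.** At a true difference of 0.15 it is about Φ((0.079 − 0.15)/0.02502) = Φ(−2.84) = 0.2%. It is largest when the true difference is midway, at 0.064: 2Φ(0.015/0.02502) − 1 = 45%.

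**7. Sensitivity to the SE.** Section 3.4 gives the SD of post-treatment values, whereas the primary analysis adjusts the change for baseline. The protocol gives no baseline correlation r. If r were 0.5 to 0.7 (an assumption), multiplying the SE by √(1 − r²) gives 0.0217 to 0.0179:

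| r | SE | Threshold against zero | Threshold against 0.03 | Success against zero at true 0.03 |
|---|---|---|---|---|
| unadjusted | 0.0250 | 0.049 | 0.079 | 22% |
| 0.5 | 0.0217 | 0.042 | 0.072 | 28% |
| 0.7 | 0.0179 | 0.035 | 0.065 | 39% |

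The thresholds move with the SE. The gap between them is always 0.03.

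**The case against.** The strongest reply is that the protocol never defines success as exceeding placebo by more than 0.03. The stated objective is only to evaluate efficacy and safety, and Δ may have been meant as a way to make the sizing more conservative. The null of zero is inferred from the usual meaning of a two-tailed test of a difference; the protocol does not state it. The planned 95% interval is exactly what is needed to compare the lower limit with 0.03. Section 3.5.3 also has a statistical analysis plan finalised before database lock, and that plan is not at hand.

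Much of this stands. A reader might infer that the margin claim is bound to go untested, or that the trial carries a 22% false positive rate. The documents support neither. The interval permits the test. Rejecting zero when the true difference is 0.03 is a correct rejection of zero, and becomes an error only if superiority by the margin is then claimed. The test against zero keeps its nominal alpha.

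What the reply does not remove is the conflict within the protocol. Section 3.4 gives the margin a clinical rationale, calls it the cut-off for a superiority trial and builds it into the powered hypothesis, while section 9 sets a significance rule without it. An interval that could be checked is not a prespecified rule, and the analysis section is detailed enough that the margin's absence is more than routine detail left for later.

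**Conclusion.** The mismatch is real: the margin defines the hypothesis used for sizing and is missing from the stated primary analysis and significance rule. The consequence concerns interpretation, not loss of power or invalid estimation. With 54 per arm and SD 0.13, the results affected are observed differences from about 0.049 to 0.079. These figures are illustrative, because the SE of the adjusted change analysis will differ; only the 0.03 width is fixed. Under the protocol's own assumed effect such a result is very unlikely (about 0.2%), so the point matters if the true effect is well below 0.15. It should be settled before unblinding, because it governs the conclusion on the sole primary efficacy outcome.

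**What to change.** Add to section 9.2.2(1): superiority by the margin is concluded only if the lower limit of the two-sided 95% confidence interval for the adjusted CT-FFR difference (QXJYG minus placebo) exceeds 0.03. A lower limit between 0 and 0.03 is reported as a difference from zero, with superiority by the margin not shown.

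Alternatively, if no margin claim is intended, remove Δ from section 3.4 and restate sample size and power against zero. The same formula without the margin gives 2 × [(1.96 + 1.64) × 0.13 / 0.15]² + 0.96 = 20.4, so 21 per group.

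The first option costs a short addition to the text and a success threshold that is higher by 0.03. It needs no more patients, since power at the assumed difference remains about 99.8% with 54 per arm. Two neighbouring errors can be corrected in the same revision: the 55 per group that does not follow from the printed inputs, and the significance rule in section 9.2.1, which is printed as P ≥ 0.05 and conflicts with section 9.

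### Section 3.4: the printed formula and inputs give 32 patients per arm, not the stated 55, so at least one of margin, effect, SD, power or n is misstated

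*Protocol*

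**What the plan says.** Protocol section 3.4 sizes the trial on post-treatment CT-FFR. It assumes that "the CT-FFR value in the control group is 0.77 and the value in the intervention group could be elevated to 0.92 after treatment", with "\sigma = 0.13$ for both two groups". The superiority margin is introduced by "Based on this, we have set the cut-off value" and given as "\Delta=0.03$ in this superiority trial"; the supporting argument is a published association of events with each 0.05 unit fall in CT-FFR. Allocation is equal, so c = 1. The error rates are "\alpha = 0.05$ (two-side test") and "a power of 95% (type II error rate of" 0.05), with quantiles 1.96 and 1.64. The formula is printed in full. The result is then given as "n_1=n_2\approx 55$ . Considering the maximum dropout rate of 10%, a total of 120 patients is needed".

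No other section of the protocol gives a different margin, effect or SD.

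**The concern.** All the inputs and the formula are on the page, so the result can be checked by hand, and it fails by a wide margin: 55 is about 72% more than 32 (55/32 = 1.72). Rounding cannot account for that.

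Section 3.4 is the only place where the protocol justifies its enrolment, its power and its superiority margin. If the figures do not fit together, an ethics committee or later reader cannot tell which margin, effect or SD the trial was sized on, or how much power it has for the effect it names. The margin matters most for interpretation. It is presented as a reasoned choice tied to a 0.05 unit of CT-FFR, and the inputs that would explain 55 include a margin above that unit.

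**Working it through.** **Inputs, all from Protocol section 3.4:** μT = 0.92, μC = 0.77 (difference 0.15); σ = 0.13; Δ = 0.03; c = 1; uα = 1.96; uβ = 1.64; dropout 10%.

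**Step 1. The plan's own formula.**

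n₁ = ((1+c)/c) × [(uα+uβ)σ / (μT−μC−Δ)]² + uα²/4

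= 2 × [(3.60 × 0.13) / (0.15 − 0.03)]² + 1.96²/4

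= 2 × (0.468/0.12)² + 0.96 = 2 × 3.9² + 0.96 = 30.42 + 0.96 = 31.38, so **32 per arm**.

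The plan's 55 is not reproduced. Without the added term, the normal approximation gives 31; a calculation based on the noncentral t gives 32. At 32 per arm the total would be 64 evaluable, and 64/0.90 = 71.1, so 72 randomised.

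**Step 2. Does a usual variant give 55?** One input is changed at a time.

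| Change | n per arm |
|---|---|
| none (as printed) | 31.4 |
| one-sided α (1.645) | 26.0 |
| no margin | 20.4 |
| Δ = 0.05 | 44.8 |
| SD pooled from the two cited values 0.10 and 0.16 (0.1334) | 33.0 |
| SD 0.16 | 47.0 |
| power 99% | 44.1 |

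None does.

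**Step 3. What does give 55?** Again with the other inputs as printed:

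- Δ = 0.06: denominator 0.15 − 0.06 = 0.09, and 2 × (0.468/0.09)² + 0.96 = 2 × 5.2² + 0.96 = 55.04.
- True difference 0.12 with Δ = 0.03: denominator again 0.09, so 55.04. This would also arise if the margin were subtracted twice.
- σ ≈ 0.173: solving for σ, √((55 − 0.96)/2) × 0.12/3.60 = 0.1733.

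**Step 4. Evaluable patients.** 120 × 0.90 = 108, or 54 per arm. In the other direction, 110/0.90 = 122.2; with equal arms, 55/0.90 = 61.1 gives 62 per arm, 124 in total.

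**Step 5. Power with 54 per arm** (normal approximation).

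Standard error = 0.13 × √(2/54) = 0.0250.

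- Printed inputs: Φ(0.12/0.0250 − 1.96) = 0.998. With 55 per arm it is also 0.998.
- Denominator 0.09 (Δ = 0.06, or difference 0.12 with Δ = 0.03): Φ(0.09/0.0250 − 1.96) = 0.949.
- Difference with 95% power against Δ = 0.03: 0.03 + 3.60 × 0.0250 = 0.03 + 0.090 = 0.12.

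**The case against.** The strongest reply is that nothing is lost in practice. On the printed inputs the error is conservative: more patients are recruited than the formula requires. The primary analysis in section 9.2.2 reports a mean difference with a 95% confidence interval and names no margin, so the value of Δ does not alter that analysis as written. Both statements are correct, and they limit the consequence to the justification of the design. They do not make the paragraph true: a headline figure contradicted by the formula printed beneath it still has to be corrected.

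A reader might also go further than the protocol allows, in three ways.

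- **That the trial was really sized on a margin of 0.06.** This fits numerically, but so do a difference of 0.12 and an SD of about 0.173. Each conflicts with something printed. A margin of 0.06 exceeds the 0.05 unit on which the margin is said to rest; 0.12 is not 0.92 − 0.77; and 0.173 is above both cited SDs, 0.10 and 0.16. The text does not decide between them.
- **That both the margin and the power are wrong.** If the margin and the other inputs stand, only the power and the required n are misstated. If 95% power at 55 per arm stands, the margin, effect or SD differs from the text.
- **That the dropout step is a second error of substance.** The figure of 55 is marked as approximate, and 120 randomised leaves 54 per arm, one fewer. That is rounding.

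**Conclusion.** The point holds. The stated 55 per arm is not the result of the printed formula and inputs, which give 32, and at least one of margin, effect, SD, power or n in section 3.4 is misstated. The protocol does not reveal which.

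If the printed inputs are taken as true, power with 54 evaluable per arm is about 99.8% at a difference of 0.15 against a margin of 0.03, where 95% is claimed; the claimed 95% belongs to a difference of about 0.12. If the denominator was really 0.09, power with 54 per arm is 94.9%, in line with the claim, but the margin or effect must then be reprinted. These powers assume SD 0.13, normal approximation, two-sided α of 0.05 and exactly 10% loss in each arm.

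A reader might infer from the mismatch that the trial is underpowered. Under its stated inputs it is not.

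**What to change.** Keep 120 randomised. Identify the inputs that produced 55 and correct section 3.4 so that margin, effect, SD, power and n agree.

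- **If the printed inputs stand:** state that the formula requires 32 per arm, and that 54 evaluable per arm gives about 99.8% power at a difference of 0.15 (or 95% at 0.12).
- **If a different margin, effect or SD was used:** print that value, justify it, and give the matching power. For a margin of 0.06 this is 94.9% with 54 per arm, and the link to the 0.05 unit of CT-FFR would need rewording.
- **In either case:** state 54 evaluable per arm, not 55, as what remains of 120 after 10% dropout.

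The cost is the wording of one paragraph. Enrolment does not change.

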### **3.5 Blinding Method**

A double-blind design is adopted. The first level is the group corresponding to each case number (e.g., Group A, Group B), and the second level is the treatment corresponding to each group (experimental group, control group).

#### **3.5.1 Blinding and Blind Envelope Retention**

Random numbers are generated using SAS statistical software package based on a stratified randomization method, and drugs are blinded and packaged according to these random numbers. The trial utilizes a double-blind, double-dummy technique, and all study drugs and control drugs should be packaged in the same manner, and blinded according to the random numbers. Both the investigational drug and the placebo should be uniformly packaged, ensuring that the appearance of the active drug and the placebo is indistinguishable. The blinding process is jointly completed by the head of the responsible clinical research unit, the sponsor, and the statistical personnel. Two copies of the blind envelopes are prepared and sealed, and they are kept by the primary research unit and the sponsor. During the trial, the blind envelope cannot be opened or read.

### 3.5.2 Emergency Unblinding

Along with the drug packaging and coding, an emergency envelope is prepared for each drug, containing the sealed information about the group assignment corresponding to the drug's code. In the event of a medical emergency, the emergency envelope (emergency unblinding) can be opened. Emergency unblinding may be considered in the following situations, but not limited to:

- a) When a patient experiences severe adverse reactions/adverse events.
- b) When a patient experiences severe complication.
- c) When urgent measures are required due to deteriorating symptoms.

In the case of an emergency requiring unblinding, the researcher must seek approval from the head of the center, and upon obtaining their signed agreement, the emergency unblinding envelope can be opened. Detailed records of the unblinding reason, time, location, and signatures must be made. Within 24 hours of unblinding, the head of the clinical research team and relevant personnel from the sponsor should be notified, and the reasons for unblinding should be explained. Cases that withdrew due to efficacy reasons should not be unblinded. Data related to unblinded cases should be kept complete.

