## ***2.5 Withdrawal criteria***

- 1) Conditions continue to worsen.
- 2) Comorbidities, complications, or special physiological changes.
- 3) Poor compliance or use of prohibited drugs.
- 4) Adverse events or serious adverse events.
- 5) Leak of blindness

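### Emergency unblinding waits for the center head's prior signature, and the protocol gives no route if that person cannot be reached in time

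*Protocol*

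**What the plan says.** Section 3.5.2 opens with a general permission: "In the event of a medical emergency, the emergency envelope (emergency unblinding) can be opened". It then lists situations, not meant to be exhaustive, in which this may be considered: severe adverse reactions or events, a severe complication, and reason (c), "When urgent measures are required due to deteriorating symptoms".

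The permission is then made conditional: "the researcher must seek approval from the head of the center, and upon obtaining their signed agreement, the emergency unblinding envelope can be opened". The reason, time, location and signatures must be recorded. The only time limit applies after the event: "Within 24 hours of unblinding, the head of the clinical research team and relevant personnel from the sponsor should be notified".

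Near its end the section adds a bar: "Cases that withdrew due to efficacy reasons should not be unblinded". Section 2.5 gives as its first withdrawal criterion "Conditions continue to worsen", and its last is loss of blinding. Section 2.5.2 names ineffective treatment among the reasons for withdrawal: "If someone withdraws due to allergic reactions, adverse events, or ineffective treatment, the investigator should provide appropriate treatment measures".

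**The concern.** An emergency envelope is useful only if it can be opened as fast as the emergency requires. Here the approval is mandatory, it comes before opening, it must be signed, and it rests with one role at each center. If that person is unavailable, the investigator must either wait or open the envelope and record a protocol deviation. The first delays information that may be wanted for the patient. The second makes a deviation out of conduct that the section was written to permit.

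The bar on efficacy withdrawals raises a lesser question. A patient may be withdrawn because the disease is worsening and may also need urgent measures. The section does not say which sentence then governs, so centers could handle such a patient differently.

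**Working it through.** No arithmetic applies to the main point. The check sets the provisions side by side.

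1. **Is the signature a precondition?** Yes. The wording is mandatory, and opening follows only once the signed agreement is in hand (Section 3.5.2).

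2. **Is there another route?** None is stated. Neither Section 3.5.2 nor the rest of the protocol mentions a deputy, verbal approval, retrospective approval, a time limit for the head's reply, or an exception when the head is absent. The 24-hour limit runs from unblinding, so it does nothing to speed the approval.

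3. **Do the triggers call for speed?** Yes, by the protocol's own definitions. Severe adverse events are a listed trigger. The severity table in Section 7.2.1 defines severe as life-threatening and calls for the drug to be stopped immediately or emergency treatment given. Reason (c) is itself limited to situations that need urgent measures.

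4. **Is care blocked?** No. Section 7.2.1 attaches no unblinding or approval condition to stopping the drug or to emergency treatment. Section 2.5 allows withdrawal for adverse events, and Section 2.5.2 requires treatment for those who withdraw because of adverse events or ineffective treatment. Under Section 4.1 both arms receive conventional treatment, with granules or placebo added. The documents name no management step that differs by arm. What waits for the signature is knowledge of the allocation.

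5. **Does oversight depend on the prior signature?** Not entirely. The record of reason, time, location and signatures, and the 24-hour notice, would remain without it. The prior signature does add one thing that later notice cannot: it can stop an unnecessary opening.

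6. **Does the bar on efficacy withdrawals conflict with reason (c)?** Only where they overlap.
   - Worsening without urgency does not meet reason (c), so there is no conflict.
   - Urgent worsening in a patient who has not withdrawn for efficacy reasons is not caught by the bar, so there is no conflict.
   - A patient withdrawn for efficacy reasons who also needs urgent measures meets both sentences. Efficacy reasons are not defined and the bar states no emergency exception, so the text leaves this case open.

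**The case against.** The best defense has four parts.

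**Care does not wait.** The investigator can stop the blinded product and treat without knowing the arm. This stands. A reader might infer that a bleeding patient goes untreated until a signature arrives. The documents do not support that: only the envelope is held up.

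**The missing deputy is silence.** Delegation and out-of-hours cover may sit in site procedures that are not shown, and nothing forbids them. This stands in part. Such procedures may exist, but the protocol does more than omit a detail. It states a condition that must be met before opening, and a site that let someone else approve would be departing from that wording.

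**Prior approval protects the blind.** This stands as a cost of changing the rule. Section 2.5 makes loss of blinding a withdrawal criterion, so an unnecessary opening might lose a participant. Section 3.4 needs about 55 per arm and plans 120 in total, a margin of 120 − 2 × 55 = 10.

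**The efficacy bar is no contradiction.** A reader might infer that any patient whose angina deteriorates is both allowed and forbidden to be unblinded. That drops the words about urgent measures from reason (c) and assumes that every worsening patient is an efficacy withdrawal, which Section 2.5 does not say. The natural reading is that lack of effect alone is not an emergency. What remains is an undefined term and a narrow overlap.

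**Conclusion.** The point holds in limited form. Section 3.5.2 makes access to the allocation depend on one person's prior signed agreement and states no route if that person cannot be reached in time. Access can therefore be delayed in the emergencies the envelope is meant for. The text does not show that unblinding would fail in every emergency; the head may often be reachable, and many emergencies can be managed without the allocation.

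The rule applies at all 3 centers (Section 3.1). How often it would matter cannot be estimated, since the protocol gives no expected number of emergencies or unblindings. No effect on the CT-FFR comparison is claimed. The conclusion assumes that the protocol's wording governs over any site procedure not shown here.

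The unclear reach of the efficacy-withdrawal bar is secondary, and confined to patients who meet both descriptions. The change is worth making because it is cheap and concerns a participant safeguard, not because the design or primary analysis is at risk.

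**What to change.** In Section 3.5.2, let the investigator open the emergency envelope without waiting for the signature when knowledge of the allocation is urgently needed. Have the center head's approval or notification documented afterwards, alongside the existing record and the 24-hour notice. This changes who may open an envelope and when approval is recorded; it sets no treatment or stopping rule.

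Reconcile the bar on unblinding efficacy withdrawals with reason (c), so that the text says which governs when a withdrawn patient also needs urgent measures.

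The cost is about two sentences of protocol text. The downside is a small risk of unnecessary unblinding. The required record would make it visible but would not undo it, and it could cost a participant under the loss-of-blinding criterion in Section 2.5. It would help to state there whether a justified emergency unblinding counts under that criterion.
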